## Abstract

**Introduction::**

Pericoronitis is a common disease in the eruption phase of third molars, sometimes debilitating, with an impact on the quality of life. The most indicated treatment in the initial phase is the irrigation for cleanliness of the region. In order to reduce the chances of systemic dissemination of the infection and antibiotics use, it is mandatory to test effective treatments in the initial phase of pericoronitis avoiding the evolution of the infectious disease. Photodynamic therapy (PDT) is an interesting alternative because it is an effective antimicrobial treatment that is easy to perform and does not select bacterial resistance. The methylene blue (MB) used in PDT has been studied in an oral formulation, which optimizes the formation of monomers increasing its antimicrobial action.

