**Objective::**

The aim of this study is to evaluate the effectiveness of PDT with MB in an astringent vehicle in pericoronitis on the initial phase in healthy patients through microbiological, clinical, and immune response. The impact of pericoronitis on oral health-related quality of life (OHRQoL) of these patients will also be evaluated.

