### Design

2.4

This is a controlled, randomized, double-blind, clinical trial:

G1—(positive control group) 32 patients with pericoronitis, irrigated with sterile saline and the PDT performed with conventional MB. The irradiation will be performed with low intensity laser λ = 660 nm, 9J per point and radiant exposure of 318 J/cm^2^.G2—(experimental group) 32 patients with pericoronitis treatment identical to G1, however the PDT will be delivered in a new formulation for oral use (patent application INPI BR1020170253902).^[19]^

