### Statistical analysis

2.7

The data will be collected, tabulated on Excel table developed for research and presented in a descriptive way. All statistics will be conducted using the SPSS 21 program package (SPSS Inc, Chicago, IL). In the first part of the results will be performed the descriptive analysis. Measures of: absolute number, mean, standard deviation, minimum value and maximum value, percentage and cumulative percentage will be used. The bacterial count will be normalized by conversion into logarithmic values will be compared by the student *t* test. In the second part, we will verify the inferential analysis for the numerical variables. Tests of Normality Skewness and Kurtosis will be used, then verification of the homogeneity of the variables. The ANOVA will be applied for repeated data, and the Spearman correlation, and the Huynh-Feldt, Greenhouse-Geisser, Box's conservative tests. If there is no normality of the sample will be used The Wilcoxon test will be used in order to compare before and after the PDT. The *P* value is set at *P* < .05 (95% level of significance). By the end of the study, randomized groups will be revealed and statistical analysis will be performed as group A or B. The meaning of A or B will be known after statistical analysis. The data will be evaluated by comparing 2 groups: experimental and control groups (gold standard).

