Another researcher will apply the red diode laser. The red light will act to improve tissue repair and decrease the periodontal inflammatory process, especially on facial swelling and trismus ^[22]^ and also will modulate the immunoinflammatory response of the host, interfering in the levels of inflammatory cytokines. Corrêa et al,^[13]^ Candeo et al,^[9]^ and Kellesarian et al^[17]^ found a reduction of the pro-inflammatory cytokines IL1-β, IL-6, IL-8, and TNF-α after the PDT. So we will try to verify if PDT will promote advantageous modulation of cytokine levels in pericoronitis.

Macrophages that are frequently found in pericoronitis are able to produce the wide range of pro-inflammatory and anti-inflammatory mediators, as well as substances that enhance pro and anti-inflammatory substances. These substances act in the development and repair of these lesions, expressing IL-1α, TNF-α, IL-6, TGF-β, and prostaglandins and cytokines that act at the beginning and regulation of inflammatory processes through the activation and differentiation of osteoclasts, activation and proliferation of fibroblasts, production of collagen and neovascularization.^[50]^ Tumor necrosis factor (TNFα) is a cell signaling protein (cytokine) involved in systemic inflammation and is one of the cytokines that make up the acute phase reaction.^[51]^ It is produced chiefly by activated macrophages, although it can be produced by many other cell types. IL1-β, IL-6, and IL-8 are interleukins that act as pro-inflammatory cytokines. IL-10 is an anti-inflammatory cytokine.

The GCF is a transudate of interstitial tissues which is produced by an osmotic gradient, and it is released into the crevicular sulcus. However, during periodontal inflammation, the main mechanism of GCF formation becomes exudative, with an increase in its flow rate, and thus volume.^[52]^ Cytokines produced by various cells are strong local mediators of inflammation.^[53]^ GCF, an exudates, harnessed from the sulcus or periodontal pocket, has been regarded as a promising medium for the detection of periodontal disease activity.^[54]^ GCF has also demonstrated a potential value to evaluate periodontal therapy efficacy.^[23]^

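### The only comparison test named for non-normal data is before versus after PDT: it does not compare the randomised arms, and such a change cannot show that PDT itself works

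*Protocol article*

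**What the plan says.** Section 2.7 (Statistical analysis) assigns a Student t test to the log bacterial count. In a second part, on numerical variables, it lists normality checks and a repeated-measures ANOVA. The non-normal branch opens "If there is no normality of the sample will be used The Wilcoxon test" and runs on, from those same last three words, as "The Wilcoxon test will be used in order to compare before and after the PDT". No rank-sum or other non-parametric test between arms is named. Spearman correlation appears, but it is not a comparison of groups.

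The section closes with a between-arm intention: "The data will be evaluated by comparing 2 groups: experimental and control groups (gold standard").

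Section 2.4 (Design) describes G1 as "32 patients with pericoronitis, irrigated with sterile saline and the PDT performed with conventional MB", and G2 as "32 patients with pericoronitis treatment identical to G1, however the PDT will be delivered in a new formulation for oral use". Section 2.5 gives saline irrigation of the sulcus to everyone. The arms therefore differ only in the MB vehicle, and no arm goes without PDT.

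The aims are nevertheless partly about PDT itself. The Abstract's Objective says "The aim of this study is to evaluate the effectiveness of PDT with MB in an astringent vehicle in pericoronitis on the initial phase", and the last paragraph of the Introduction repeats this aim for the oral formulation. On cytokines, the Discussion says "we will try to verify if PDT will promote advantageous modulation of cytokine levels in pericoronitis".

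**The concern.** Two related problems follow.

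1. **Wrong contrast in the non-normal branch.** Randomisation supports a comparison of G2 with G1. A Wilcoxon test of before against after measures change over time within patients. Whether it is pooled or run per arm, it does not estimate or test the difference between vehicles. An outcome that fails the normality check, for example a skewed cytokine or OHIP-14 score, would leave the plan with no named test of the trial's own question.

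2. **Attribution to PDT.** Change from T1 to T3 in either arm combines PDT, irrigation, natural course and regression to the mean. The Abstract's own Introduction says of irrigation "The most indicated treatment in the initial phase is the irrigation for cleanliness of the region", so irrigation cannot be assumed inert. A significant before-after test would look like support for the PDT-effect aims without being so.

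At stake is a report that rests on change from baseline, or on a contrast of two within-arm p-values. Neither uses the randomisation.

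**Working it through.** The plan gives no figure on this point to reproduce. The total of 64 patients in section 2.1 does not enter the argument.

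**Step 1. Match each named method to the contrast it can give.**

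| Method in section 2.7 | Contrast |
|---|---|
| Student t test on log count | Between arms, if used as an independent-samples test |
| Repeated-measures ANOVA | Between arms, if group is a factor |
| Wilcoxon (non-normal branch) | Before versus after, as stated |

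The first two can answer the randomised question. The third cannot, so the defect is confined to the non-normal branch.

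**Step 2. What a per-arm reading would do.** Suppose the vehicles are identical and each arm has probability p of a significant before-after change. The arms are independent, so

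P(exactly one arm significant) = 2p(1−p).

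- p = 0.5: 2 × 0.5 × 0.5 = 0.50 (the maximum of the formula)
- p = 0.8: 2 × 0.8 × 0.2 = 0.32
- p = 0.95: 2 × 0.95 × 0.05 = 0.095

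**Step 3. Simulation.** Assumptions: 32 per arm (section 2.4), normal change scores with SD 1, the same mean improvement in both arms, no arm difference, two-sided 5% tests, 3,000 runs per row. The improvement sizes are assumed, because the document gives none.

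| Common improvement (SD of change) | Pooled before-after Wilcoxon significant | Both arms significant | Exactly one arm significant | Mann-Whitney on change, between arms |
|---|---|---|---|---|
| 0 | 4.6% | 0.2% | 8.8% | 4.4% |
| 0.3 | 62.9% | 13.6% | 44.8% | 4.9% |
| 0.5 | 97.2% | 60.3% | 33.9% | 5.1% |
| 0.8 | 100% | 97.8% | 2.2% | 5.0% |
| 1.0 | 100% | 100% | 0.0% | 4.7% |

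Cross-check at 0.5 SD: per-arm p = 0.603 + 0.339/2 = 0.7725, and 2 × 0.7725 × 0.2275 = 0.351, close to the simulated 0.339.

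The before-after test responds to any change that both arms share, whatever its cause. The between-arm test stays near 5%, as it should when the vehicles do not differ.

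**Step 4. Attribution.** Sections 2.4 and 2.5 give both arms the same irrigation and laser PDT. No contrast in the trial, within or between arms, varies PDT. This holds whether or not normality holds.

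**The case against.** The strongest reply is that section 2.7 is badly edited rather than wrongly designed. The fallback sentence breaks in the middle and a test name may have dropped out. The Wilcoxon could then be an extra test of time beside an unnamed fallback. The section also says that analysis is by group A or B and that the two groups will be compared, and a condensed article may leave the exact rank test to an analysis plan that is not shown.

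Much of this stands, and it rules out several stronger readings that a reader might infer:

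- *The plan abandons the randomised comparison.* It does not. The between-arm intention is stated, and the parametric methods can deliver it.
- *The primary outcome is lost.* This is not established. The t test on the log count is stated before the part that contains the normality checks, and nothing clearly ties the fallback to it. For pain, the Discussion expects parametric tests.
- *The false-positive rate is 50%.* That is the maximum of 2p(1−p), under a per-arm decision rule that the protocol never states. In the simulation, discordance runs from 45% down to 0% as the common improvement grows from 0.3 to 1.0 SD.
- *The vehicle question is missing.* The Discussion states it twice, and G1 is labelled a positive control.
- *The gold-standard label contradicts the statement on irrigation.* Both arms are irrigated, so the label is an editorial matter and changes no analysis.

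The reply does not remove the core. The article names a test and states its purpose, and that purpose is the wrong contrast for a two-arm randomised question. This is more than omitted detail. Section 2.1 also sizes the trial with a paired t test for two separate arms, so the mix of paired and between-arm thinking is not confined to one sentence.

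**Conclusion.** The concern holds in a limited form. In section 2.7 the only comparison test named for non-normal data does not compare G1 with G2, so outcomes sent to that branch have no named test of the randomised comparison. How many outcomes this affects depends on the data and on what the garbled sentence was meant to say. The discordance figures of 50%, 32% and 9.5% are illustrations that assume identical vehicles and a per-arm reading.

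The attribution point is independent of normality and follows from the design alone: a before-after change cannot show that PDT itself works. A reader might infer that the authors plan to treat such a change as proof of efficacy. No sentence says so, but the Objective, the Introduction's aim and the cytokine sentence in the Discussion are worded so as to invite it.

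**What to change.** 1. **Section 2.7.** Repair the sentence so that the non-normal branch uses a between-arm test: Mann-Whitney on the T3 minus T1 change, or rank ANCOVA of T3 on T1. Report the Hodges-Lehmann difference with its 95% CI. State whether the branch covers the log bacterial count.
2. **Same section.** Keep the signed-rank test as within-arm description only, with no inference drawn from one arm being significant and the other not.
3. **Abstract (Objective), last paragraph of the Introduction, and the cytokine sentence in the Discussion.** Restate the objective and conclusions as new versus conventional MB vehicle within PDT, and say that before-after changes are descriptive.

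The cost is wording and a few lines of analysis code. No extra patients, visits or assays are needed, and the change can be made before the A/B code is broken. The trial gives up only a claim about PDT itself that its design cannot support.

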## Discussion

3

The main rationale for conducting this study is to verify a possibility of treating pericoronitis with a low risk alternative. Other reasons are to suppress or reduce the quantity of antibiotics medications and to test if the new oral formulation with MB is more effective on bacterial reduction.

The primary outcome will be the presence and quantity of bacterium *T forsythia*, and secondary: pain, swelling, trismus, GCF and salivary cytokines, OHRQoL and position and classification of the lower third molars, to avoid bias the measurement of all these outcomes should be standardized.

The bacterium *T forsythia* plays an important role in the development of clinical symptoms of pericoronitis.^[28,29]^ The presence and quantity of *T forsythia* increase in 8 times the risk of developing pericoronitis, when compared to individuals without it.^[28,30,31]^ This bacterium was also associated with the development of pericoronitis in other studies and was present in 40% of their samples.^[32–35]^ Thus, it will be important to measure it properly and quantify this association.^[28]^

PDT causes non-toxic death, leading to destruction of the cell wall and consequent death of the microorganisms. The capacity of PDT to kill bacteria has been studied by several authors; Fontana et al^[16]^ found that bacteria did not reduce to the same degree as has been reported for treatment with antibiotics.

PDT is effective in destroying periodontal pathogens,^[36]^ since most oral bacteria do not absorb the visible light, it is necessary to use the PS, which must act for a period before irradiation.^[37]^

The PS binds to the cell of the microorganism because it needs to bind to negative charges and the membrane of the microorganism has more negative charge than the membrane of the host cell.^[38]^ Gram-negative bacteria induced the dye dimerization more intensely than gram-positive bacteria.^[39]^ The membrane of microorganism are always negatively charged, so the positively charges PS attach and/or aggregate to them and end up interfering on benefits of PDT process.^[40]^

The issue of QoL has largely been neglected within the practice of oral-maxillofacial surgery.^[41]^ OHRQoL is defined as an individual's assessment of how the following elements affect well-being. Magraw et al ^[42]^ concluded that the impact of pain on patients with pericoronitis leads to a worsening OHRQoL, which can influence on the decision of third molar extraction.^[43,44]^ The OHIP-14 questionnaire asks about the adverse impacts of oral conditions on well-being.^[45]^ QoL outcomes may be as important as clinical signs when decisions are rendered regarding third molar extractions.^[26,46]^

For pain measurement, a VAS will be included as the main instrument for assessing the patients’ complaint regarding pain. It is graduated in centimeters, which allows the use of parametric tests, which improves accuracy of data analysis.^[28,47,48]^ Pain affects most domains of QoL,^[49]^ which depends on the extent, duration, acuteness, intensity, affectivity, and meaning of the pain, as well as the underlying disease and the individual's characteristics.^[26]^

In order to avoid bias, and to try to eliminate subjectivity factors of pain and quality of life, the same researcher will measure all outcomes and they should be standardized using established methods as VAS and OHIP-14.

Classifications are used to predict the surgical degree of difficulty, and to evaluate the risk of pre and postoperative complications.^[25]^ Pell and Gregory and Winter techniques,^[26]^ are the most common techniques to evaluate tooth position. It evaluates the tooth depth position in the vertical direction (relative to the occlusal plane and in relation to the neck of the adjacent second molar) and horizontally (as it evaluates the position of the tooth in relation to the ramus of the mandible). In order to classify the position of a tooth, the position of the teeth will be evaluated through panoramic radiography, according to the classification of Pell and Gregory and Winter ^[26]^ performed only by 1 evaluator, following the criteria of imaginary lines as proposed by Almendros-Marques et al.^[27]^

Another researcher will apply the red diode laser. The red light will act to improve tissue repair and decrease the periodontal inflammatory process, especially on facial swelling and trismus ^[22]^ and also will modulate the immunoinflammatory response of the host, interfering in the levels of inflammatory cytokines. Corrêa et al,^[13]^ Candeo et al,^[9]^ and Kellesarian et al^[17]^ found a reduction of the pro-inflammatory cytokines IL1-β, IL-6, IL-8, and TNF-α after the PDT. So we will try to verify if PDT will promote advantageous modulation of cytokine levels in pericoronitis.

Macrophages that are frequently found in pericoronitis are able to produce the wide range of pro-inflammatory and anti-inflammatory mediators, as well as substances that enhance pro and anti-inflammatory substances. These substances act in the development and repair of these lesions, expressing IL-1α, TNF-α, IL-6, TGF-β, and prostaglandins and cytokines that act at the beginning and regulation of inflammatory processes through the activation and differentiation of osteoclasts, activation and proliferation of fibroblasts, production of collagen and neovascularization.^[50]^ Tumor necrosis factor (TNFα) is a cell signaling protein (cytokine) involved in systemic inflammation and is one of the cytokines that make up the acute phase reaction.^[51]^ It is produced chiefly by activated macrophages, although it can be produced by many other cell types. IL1-β, IL-6, and IL-8 are interleukins that act as pro-inflammatory cytokines. IL-10 is an anti-inflammatory cytokine.

The GCF is a transudate of interstitial tissues which is produced by an osmotic gradient, and it is released into the crevicular sulcus. However, during periodontal inflammation, the main mechanism of GCF formation becomes exudative, with an increase in its flow rate, and thus volume.^[52]^ Cytokines produced by various cells are strong local mediators of inflammation.^[53]^ GCF, an exudates, harnessed from the sulcus or periodontal pocket, has been regarded as a promising medium for the detection of periodontal disease activity.^[54]^ GCF has also demonstrated a potential value to evaluate periodontal therapy efficacy.^[23]^

The composition of this fluid resembles that of serum, and the intensity of its flow has been shown to vary as a function of gingival inflammation. There is a wide variation in the methods of collection, storage, and analysis along with elusion protocols making the values alter based on this variation.^[54]^ Kinney et al^[23]^ concluded that the greatest degree of sensitivity was noted with GCF biomarkers compared to saliva biomarkers on the identification of periodontal disease progression, reason why it will be used this method in this study, and it will be compared to salivary cytokines.

MB was chosen as a PS. MB absorbs well the red light^[14]^ and it is the most commonly used PS in dentistry for antimicrobial action.^[6]^ The 3 minutes pre-irradiation time of MB was established based on Joseph et al^[12]^ research. Any decrease of penetration of MB in biofilm may be attributed to a reduced action of PDT,^[16]^ thus an adequate pre-irradiation time is desirable.

It is difficult to predict the efficacy of PS as many factors may contribute to their cellular photoactivity, which is usually related to properties of their monomers species.^[39]^ A decrease in photochemical effects may occur due to dimerization of MB.^[6]^ MB has a tendency to aggregate, also called metachromacy, which is the property of forming dimer or higher aggregation products upon increasing dye concentration or changing the microenvironment (e.g., high ionic strength). It interacts with the anionic macromolecule lipopolysaccharide resulting in the generation of MB dimmers.^[16]^ The absorption spectrum of MB is changed upon aggregation, altering the wavelength of highest absorption to lower wavelengths.^[11]^ Bergmann and Konski^[55]^ showed that the absorption spectrum of monomer and dimer are different. Monomer absorbs light at the wavelength of 660 nm and the dimer at 590 nm. Besides, depending on its ground state monomer/dimmer equilibrium the photochemical properties which can be shifted from type II to type I.^[10,56]^ This fact can interfere with the antimicrobial potential of PDT, since it decreases the formation of singlet oxygen.^[57]^ Here, by changing the MB vehicle, the study aims to verify if the reduced aggregation improves the antimicrobial effect.

Some authors believe that a wavelength of 633 to 670 nm is the best option for laser therapy.^[58,59]^ It is necessary, a wavelength which achieves depth and leads to a triple excitation state of PS.^[7]^ This wavelength will be used and seems to be sufficient for our study.
